### Village doctors

Since 2018, the village doctor responsibility system has been implemented in Liangshan Prefecture. The local government has assigned one village doctor, managed by the Health Commission, to each village. Most of the village doctors are from the local communities and recently graduated from the local health technical school that provides students basic medical training. They are predominately young, with an average age of 20 to 25 years. They grew up in the Yi ethnic environment and received a general education in Mandarin Chinese under the state-run public education system administrated by the Chinese Ministry of Education. Therefore, the village doctors are proficient in both Mandarin Chinese and the Yi ethnic group’s language, allowing them to communicate freely with the Yi villagers, serving as a bridge connecting modern life and traditional Yi culture.

The daily work of is mainly divided into two categories: providing public health services and delivering primary care and treatment. Rural doctors are responsible for supplying essential medical services and educational campaigns on various diseases to rural residents. Rural doctors must promptly report suspected infectious disease epidemics to county-level medical institutions and handle public health emergencies per regulations. The health administration department may request village doctors to collect specific health data from the residents.

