### Randomization and allocation

Randomization is done by the research team at the cluster level using a stratified randomization method, with each village defined as a cluster. First, each village will be assigned a number. Next, the cillage numbers will be extracted and randomized into three groups in a 1:1:1 ratio: (1) The “Control” group without any mobile-based message intervention; (2) “Intervention A” with village doctors delivering HIV-related intervention messages to the participants and receiving a standardized monetary compensation, and (3) “Intervention B” with village doctors delivering HIV-related intervention messages to the participants and receiving a monetary compensation, the amount of which will depends on how well the participants perform during the intervention.

In the entire process of data collection, management, and analysis, the staff members will not be informed of the randomization scheme. The data analyst will also not be informed until the results of the analysis obtained. Only the research team staff responsible for message delivery will be aware of which villages are assigned to each experimental group. The village doctors will not know the experimental group to which they belong or the differences between the three groups; this will prevent them from comparing their responsibilities, tasks, and monetary compensation with others in a different group, which could result in bias or a change in attitude toward their assignment. Furthermore, the village doctors will not be allowed to discuss with the participants of any group information about which the doctors have speculated.

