### Preparation for the intervention

The tools that will be used for the intervention are WeChat and the Chinese Version of TikTok (Douyin in Chinese). WeChat is an instant messaging application that is widely used in China for communication. The number of active Wechat users reached 1.27 billion in 2021 Q4 (with a total population of 1.41 billion), making it convenient for distributing HIV-related information via text, voice, graphics, and video messages. The Chinese Version of TikTok is the most popular short video-sharing platform in China, and it can be used to share HIV-related educational videos with the study participants. A data collecting application alled Interviewer will be used to collect demographic and economic information from the participants. The use of these applications facilitates the management of stakeholders and ensures effective dissemination of information.

The research team will create a WeChat account with three group chats: “Control,” “Intervention A,” and “Intervention B.” Doctors in the control and intervention groups are required to add the research team’s WeChat account as a contact, enter the specified intervention group chat, and create a new group chat to connect with participants in their village. HIV-related intervention content will be delivered from the research team to the village doctors through their assigned intervention group chat and then forwarded to the participants by the village doctors in the group chat they previously created. The research team will also create two accounts for the Chinese Version TikTok, representing “Intervention A” and “Intervention B.” Village doctors and participants in the intervention groups are required to follow their corresponding accounts for the Chinese Version TikTok. The research team will post identical HIV-related short educational videos on both accounts, and the village doctors will share the videos with the participants in the WeChat group. The research team will monitor and compare the numbers of views and likes each account receives as an indicator of the effectiveness of the village doctors in promoting the videos to the participants in the two intervention groups.

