Before implementing the study, all the village doctors will receive 10 four-hour training sessions on the participant recruitment process, data collection procedures, intervention modules, answers to frequently asked questions, use of intervention tools, and work quality expectations. To protect the participants’ privacy and confidentiality, the research team staff will compile a unique ID for each participant to hide their personal information, including name, national identification number, and phone number during the data processing stage.

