### Intervention modules

The experimental intervention method involves delivering mobile-based HIV-related messages in the form of texts, pictures, audio, and videos using WeChat and the Chinese Version of TikTok to improve the villagers’ HIV-related health literacy and protect them from AIDS infection.

The “Control” group participants will not receive the mobile-based intervention delivered by WeChat and the Chinese Version of TikTok. They will receive general disease-related information from the AIDS public health campaign and mass media such as TV, newspapers, and internet.

In addition to receiving general information from mass media and campaigns, the participants in the “Intervention A” and “Intervention B” groups will receive HIV/AIDS awareness-raising and behavior-related cyclical messages delivered by the village doctors on a biweekly basis for 18 months. Participants who are illiterate in Mandarin Chinese or have difficulty understanding the content of the messages can consult their village doctors on WeChat in the village group chat or in a private one-on-one conversation. They may request a translation of the message into the Yi ethnic group’s language or ask the doctor to clarify and explain its content.

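### Control-arm village doctors are trained on the intervention content, which risks diluting the control versus A/B knowledge contrast

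*Protocol article*

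**What the plan says.** On training, Preparation for the intervention says that "all the village doctors will receive 10 four-hour training sessions on the participant recruitment process, data collection procedures, intervention modules, answers to frequently asked questions", and the same list goes on to the use of the intervention tools. The preceding paragraph of that section covers the control arm explicitly: "Doctors in the control and intervention groups are required to add the research team’s WeChat account as a contact, enter the specified intervention group chat". Each doctor, control included, must then "create a new group chat to connect with participants in their village".

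On the control condition, Intervention modules says: "The “Control” group participants will not receive the mobile-based intervention delivered by WeChat and the Chinese Version of TikTok". It continues: "They will receive general disease-related information from the AIDS public health campaign and mass media such as TV, newspapers, and internet". Village doctor incentives and performance monitoring adds that control doctors send no mobile-based HIV messages and are paid only for completed questionnaires.

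On the doctors' ordinary work, Village doctors says: "Rural doctors are responsible for supplying essential medical services and educational campaigns on various diseases to rural residents".

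On restrictions, Randomization and allocation says that "The village doctors will not know the experimental group to which they belong or the differences between the three groups", and that "the village doctors will not be allowed to discuss with the participants of any group information about which the doctors have speculated". The one limitation listed in the Discussion is contact with participants in other studies.

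**The concern.** What is taught in training is close to what is scored. According to Villagers' baseline questionnaire, the HIV Related Knowledge Scale covers facts, key populations, transmission, symptoms, testing, treatments, laws and harmful consequences. Those are the subjects of the eight modules. A control doctor leaves training able to explain the material on which control participants will be tested, and explaining disease to villagers is already part of the job. Because doctors are not told how the arms differ, a control doctor has no reason to hold back.

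Any knowledge gained this way in control villages is subtracted from the difference between control and the intervention groups, which is the first primary outcome. A small or null difference could then mean that messaging does not work, or that control villages received part of the same content by another route. The listed limitation does not cover this route, and training given before the study starts cannot be undone at analysis.

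**Working it through.** **1. Is control exempt anywhere?** Reading the sections together:
- Training: all doctors, with modules and FAQ answers named, and no exemption in any section.
- Mobile messages in control: excluded in Randomization and allocation, Intervention modules, and Village doctor incentives and performance monitoring.
- Face-to-face education or answering questions in control: not addressed.
- Restriction on what doctors may say: limited to their speculation about the groups; HIV content is not mentioned.

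The gap is therefore informal and in-person transfer. Delivery of the modules by mobile phone in control is already ruled out.

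**2. The plan's own figures** (Sample size calculation: 90% power, two-sided α = 0.05, 66 clusters and 1,056 participants per arm, 80% retention, 20 per cluster, 3,960 in total):
- 1,056 / 66 = 16 retained per cluster
- 16 / 0.80 = 20 recruited per cluster
- 66 × 20 × 3 = 3,960

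This arithmetic reproduces. The 66 clusters cannot be re-derived, because the section gives no effect size, standard deviation or intracluster correlation.

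**3. Effect of dilution, pairwise (one intervention arm against control).** Take the design to have its stated 90% power. The planned effect divided by its standard error is then 1.960 + 1.2816 = 3.2415. If control villages gain a fraction c of the effect, the difference shrinks to (1 − c) of its value:
- power = Φ(3.2415(1 − c) − 1.96)
- clusters per arm to restore 90% = 66 / (1 − c)², rounded up

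Neither formula needs the unreported quantities. The value of c is an assumption, since the documents give none.

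| c (assumed) | 3.2415(1 − c) − 1.96 | Power | Clusters per arm for 90% |
|---|---|---|---|
| 0 | 1.28 | 90% | 66 |
| 5% | 1.12 | 87% | 74 |
| 10% | 0.96 | 83% | 82 |
| 20% | 0.63 | 74% | 104 |
| 30% | 0.31 | 62% | 135 |

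**4. The same with A and B pooled** (assumption: 132 against 66 clusters, equal variance). The variance factor changes from 1/66 + 1/66 = 4/132 to 1/132 + 1/66 = 3/132. The standardised effect therefore becomes 3.2415 × √(4/3) = 3.743:
- c = 0: Φ(3.743 − 1.96) = Φ(1.78), about 96%
- c = 20%: Φ(2.994 − 1.96) = Φ(1.03), about 85%
- c = 30%: Φ(2.620 − 1.96) = Φ(0.66), about 75%

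In either form the expected difference is understated by the fraction c.

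**The case against.** A reader might infer that the training does contaminate control villages and that nothing in the plan prevents it. The documents do not support that. They show an opportunity, and no section has control doctors pass the content on. A control doctor who forwarded modules on WeChat would breach the arm as defined. Control doctors also have no TikTok account to promote and no payment for messaging, whereas A doctors receive 200 CNY per month and B doctors 0 to 400 CNY. This narrows the concern but does not close it, because none of it touches conversation in person or replies to questions.

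It can also be said that doctor-led education belongs to the comparator. Control receives the AIDS campaign, campaigns are part of doctors' work, and A and B receive messages on top. That stands: only the extra education caused by the training counts as dilution. Common training could even be meant to isolate the effect of messaging, but then the control condition is a trained doctor without messages, and Intervention modules does not describe it so.

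Identical training may help keep doctors unaware of their arm. The article does not give this reason, and its group chats are already named Control, Intervention A and Intervention B, so that protection is thin. Splitting the training still has a cost here.

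Finally, this is a condensed article, and instructions to doctors may sit in a fuller document. That could explain a missing instruction. It does not change the stated rule that all doctors are trained on the modules.

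**Conclusion.** The concern holds as a risk of dilution toward the null, of unknown size, in control versus A/B. The stated training rule and the stated control condition do not fit together, and the remaining safeguards leave in-person transfer open.

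The power figures are scenarios. They rest on an assumed c, on the stated 90% power being correct, and on the choice between a pairwise and a pooled comparison, which the description of the primary outcome leaves open. At c = 5% the pairwise loss is about 3 percentage points; at 30% it is about 28.

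Two wider readings should be avoided. The second primary outcome, A versus B, does not use the control arm and is not diluted by this route. And because this bias runs toward the null, it would not by itself undermine a positive control versus A/B result; it would make the effect look smaller and a null result hard to interpret.

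**What to change.** Divide the training by content. Keep the recruitment, data-collection and conduct sessions common to all doctors. After randomisation, give the module, FAQ and intervention-tool sessions to A and B doctors only, without describing the other arms. Offer them to control doctors once the 18-month survey is complete.

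The cost is a change to the training schedule, with fewer hours for control doctors during the trial. The downside to state openly is that different training content may make the arms easier for doctors to guess, which pulls against the blinding described in Randomization and allocation.

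If common training is kept, three changes are needed: state that the control condition includes doctors trained on the modules; instruct control doctors not to disseminate module content; and record, in all arms, the HIV information that participants received from their doctor, so that the dilution can be examined. This costs an added instruction and a few survey items.

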### Intervention modules

The experimental intervention method involves delivering mobile-based HIV-related messages in the form of texts, pictures, audio, and videos using WeChat and the Chinese Version of TikTok to improve the villagers’ HIV-related health literacy and protect them from AIDS infection.

The “Control” group participants will not receive the mobile-based intervention delivered by WeChat and the Chinese Version of TikTok. They will receive general disease-related information from the AIDS public health campaign and mass media such as TV, newspapers, and internet.

In addition to receiving general information from mass media and campaigns, the participants in the “Intervention A” and “Intervention B” groups will receive HIV/AIDS awareness-raising and behavior-related cyclical messages delivered by the village doctors on a biweekly basis for 18 months. Participants who are illiterate in Mandarin Chinese or have difficulty understanding the content of the messages can consult their village doctors on WeChat in the village group chat or in a private one-on-one conversation. They may request a translation of the message into the Yi ethnic group’s language or ask the doctor to clarify and explain its content.

The content of the intervention is divided into eight modules, as shown in Fig. 2, along with the order of message delivery. Each module serves a unique purpose and function. (1) The basic HIV facts module mainly introduces basic information about HIV, such as its concept, origin, mechanism of action, survival rate, harmful damages to the human body, current global impact, and more. (2) The key populations module presents information on groups at higher risk of HIV/AIDS infection (e.g., MSM, IDUs, sex workers, and transgender people) and their associated characteristics to capture the participants’ attention and remind them to take protective measures if they are engaged in related work or have related behaviors. (3) The HIV transmission module provides information on the ways the virus can and cannot be transmitted and discusses the corresponding prevention methods. As one of the most critical parts of the intervention, this module includes three sub-modules with two topics each (Fig. 2). The transmission via sexual intercourse sub-module will highlight the knowledge, attitudes, skills, and values that lead to safer sex and introduce male and female condoms for defense against HIV and the correct ways to use them. The transmission via blood sub-module will introduce how contaminated blood transfusion, needle-sharing, needlestick injuries, open wound contamination, and other incidents lead to HIV infection. The sub-module will also provide an overview of the health complications and increased risk of HIV infection associated with drug use and emphasize China’s laws that regulate the manufacturing, trafficking, and usage of illicit substances. The mother-to-child transmission sub-module will share guidelines on the use of antiretroviral treatment during pregnancy, childbirth, and breastfeeding and present recommendations on breastfeeding for HIV-positive mothers to protect the infant’s health. (4) The HIV symptoms module introduces HIV-positive patients’ symptoms at different stages of the disease, the cirus's destruction of the body’s immunity, and the importance of seeking professional consultation when similar symptoms arise. (5) The HIV testing module includes reminders for the villagers to get tested regularly for HIV and direct them to available HIV self-tests, testing facilities and community centers, and testing procedures in Liangshan. (6) The HIV treatment module delivers messages on current HIV treatments and specific guidelines for various age groups. (7) The HIV laws module educates the participants on China’s HIV-related laws that protect the public and HIV/AIDS patients. (8) The harmful consequences module draws local villagers’ attention to the severe negative impacts of HIV/AIDS on public health, family, society, and the economy.

**Fig. 2 Fig2:**
[figure not shown]
Content and flow of message delivery

### Village doctor incentives and performance monitoring

For both the control and intervention (A and B) groups, the village doctors will receive a monetary reward for every questionnaire the participants fill out. In the “Control” group in which village doctors do not deliver any mobile-based HIV-related intervention messages, the monetary reward for participants’ completion of questionnaires is the village doctors' only financial incentive.

For the “Intervention A” group, in addition to the reward from participants completing the questionnaires, the village doctors will also receive a standardized monetary compensation of 200 CNY per month for sending the mobile-based HIV-related intervention messages to the participants. The research team will randomly select, contact, and conduct phone interviews with participants every month to assess the village doctors’ work performance. During the phone interviews, participants will be questioned on the following: (1) the village doctors’ completion of the assigned tasks, determined by whether the participants received effective HIV-related information transmission on a biweekly basis; (2) their understanding of key knowledge points; and (3) their satisfaction with the doctors’ attitude, competence, and willingness to explan and clarify the messages. The phone interviews will be recorded for subsequent analysis.

For the “Intervention B” group, in addition to the reward for participants completing the questionnaires, the village doctors will also receive a varying amount of monetary compensation, ranging from 0 to 400 CNY, for sending the mobile-based HIV-related intervention messages to the participants. Intervention B’s financial incentive is designed to encourage and empower village doctors to perform their duties more efficiently and enthusiastically to obtain the highest reward. Similar to Intervention A, the research team will randomly select participants for monthly phone interviews. During the phone interviews, participants’ answers to the questions in each of the three portions of the interview assessment will be scored: (1) the village doctors’ completion of the assigned tasks accounts for 30 points, (2) the villagers’ understanding of key knowledge points accounts for 50 points, and (3) participants’ satisfaction with the doctors’ attitude, competence, and willingness to explain and clarify the messages accounts for 20 points. A participant may score anywhere from 0 to 100 points. If the average score of all the selected participants from one village is 100 points, their assigned village doctor will receive 400 CNY per month. Scores lower than 100 will correspond to a lesser amount of money (e.g., a score of 50 points corresponds to 200 CNY per month).

### Outcomes measures

#### Primary outcomes

One of the study’s primary outcomes is HIV-related knowledge improvement, which is obtained by calculating weighted scores for the indicators in the HIV Related Knowledge Scale to represent the participants’ and their family members’ level of knowledge measured by the baseline and follow-up questionnaires. The research team will compare the control group and the two intervention groups to investigate whether the groups receiving the mobile-based HIV-related health education develop a deeper understanding of HIV-related knowledge than the control group which did not receive the intervention. For the second primary outcome, the research team will compare “Intervention A” and “Intervention B” to determine what type of financial reward, standardized compensation or participant performance-based compensation, is more effective at incentivizing village doctors to deliver and promote the content of the intervention. The difference between the cost-effectiveness and the participants’ HIV-related knowledge improvement of the two groups will be used to evaluate which intervention yields a more effective outcome.

